### Study Duration and Sample Size Calculation

This study’s duration will be 2 years. The sample size for the various components of the study is as follows. (1) A total of 200 community members (100 for each language per study area) will be included in the cross-cultural validation of the Explanatory Model Interview Catalogue Community Stigma Scale (EMIC-CSS) and Social Distance Scale (SDS), while 100 persons affected by leprosy (50 for each language per study area) will be included in the cross-cultural validation of the Internalized Stigma of Mental Illness (ISMI) scale and Rosenberg Self-Esteem Scale (RSES; see below). (2) A total of 770 community members will be included in the baseline and follow-up questionnaire interviews. This means a random sample of at least 385 persons in Taraba State (northern Nigeria) and at least 385 persons in Cross River State (southern Nigeria), which will consist of 114 in the audio intervention group, 114 in the written material intervention group, and 157 in the control group in each region.

This RCT will have three arms: (1) an audio-delivered intervention group, (2) a written material intervention group, and (3) a control group. The sample size calculation is based on 2 calculations. The intervention group calculation is based on an estimate of the difference in knowledge improvement between the audio-delivered intervention and the written material intervention groups. We used data from a perception study in India. In this study, postintervention scores improved by 12.5% after a poster intervention and community meetings. We estimate that the effect of posters alone would be an increase of 10%. We want to be able to detect an improvement of at least 15% between the audio-delivered and the written material intervention groups. The sample size of the intervention group is therefore based on a proportion 1 of 10 (estimated percentage of improvement in knowledge of leprosy in the written intervention group) and a proportion 2 of 25 (ie, an improvement of 15% or more). With a power of 80%, a significance level of .05, and a 15% loss to follow-up, 114 participants are needed in each intervention group.

We expect an increase of 2% in the knowledge score in the control group. The control group calculation is therefore as follows: proportion 1:10, proportion 2:2, power 80%, significance .05, and 15% loss to follow-up, resulting in 157 participants.

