### Participant Recruitment and Follow-Up

Persons affected by leprosy and community members will be selected based on purposive sampling. They will develop the content of the interventions. This is therefore, ideally, a diverse group of people who represent multiple perspectives. We will select participants based on purposive sampling to ensure adequate representation of age, gender, and villages.

The intervention will be implemented in North and South Nigeria, 2 areas that are very different. Therefore, we will cluster-randomize the interventions to ensure comparable groups are included in both areas. There are three different “groups” in each site (North and South): (1) the audio-delivered intervention, (2) the written materials intervention, and (3) no intervention (control group).

We will select 3 LGAs in North and South Nigeria (6 in total); each LGA will have either the audio-delivered or the written intervention or be a control group. The three LGAs per area will be selected based on their similarity in terms of literacy rate and endemicity of leprosy.

The interventions will be randomly allocated to clusters (LGAs) based on a random numbers list. This is a 2-stage random sampling. We will select a random sample of LGAs and a random sample of participants within each LGA. The participants in each LGA will be selected using the “spin the bottle” approach: a bottle will be spun in front of the most central place in the village (rural area) or neighborhood (urban area); the direction the bottle points at is the direction we start walking and counting. The first house to be included is selected by casting a die. Participant selection will be done by proportional sampling among the clusters. We will include the same participants at baseline and follow-up (a paired sample). This study protocol is reported in accordance with the SPIRIT statement (see checklist in Multimedia Appendix 1). The timeline schedule for participants during the study period is represented in Table 1, and a schematic description of the study flow chart is depicted in Figure 1.

**Table 1 table1:** Study schedule for enrollment, intervention, and assessment.

Schedule				Study period and time point										
				Enrollment		Allocation		Postallocation						Close out
				t_–1_		t_0_ (month 0)		t_1_ (baseline)		t_2_ (intervention)		t_3_ (6 months follow-up)		t_4_

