### Data Management and Data Analysis

Quantitative data collection will be done using electronic forms developed in the Open Data Kit, and all data will be securely stored in the cloud with access only to the research team. The recordings of the in-depth interviews and FGDs will be transcribed to the local languages, translated to English, and analyzed by 2 independent researchers using open, inductive coding and content analysis. Similar phrases with recurring themes will be coded in NVivo (QSR International). Quantitative data will be collected in the KoboCollect (Kobo Inc) mobile phone app. Data analysis will be done in the software package SPSS Statistics (SPSS Inc). Simple descriptive methods will be used to generate a demographic profile of the study sample. Differences between participants in the groups (audio, written materials, and control groups) will be evaluated using the Mann-Whitney *U* test or 1-tailed *t* test for continuous variables and the chi-square statistic for categorical variables. The mean (SD) or median (IQR), depending on the distribution of the data, of the total scores of the scales used will be calculated per intervention area. Stepwise multivariate regression with backward elimination will be done to examine what factors will have an independent effect on the outcomes. We will calculate the percentage change and corresponding 95% CI before and after the interventions are implemented and the statistical significance of this difference using a z test for differences between proportions. Effect sizes will also be calculated. If necessary, we will correct for differences in demographic information between study arms using quantile regression. We will compare the differences in follow-up assessment between the audio-delivered and written interventions. The knowledge gaps, beliefs, misconceptions, fears, etc identified in the baseline study will be summarized into a narrative review and will be used by the persons affected by leprosy group as input for the development of the content of the interventions. The most appropriate modes of delivery will be determined based on the communication needs assessment that will be conducted as part of the baseline study. The interventions will be developed using participatory methods.

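### A paired before-after change is tested with a two-proportion z test, and no listed analysis is said to use the baseline outcome or to compare improvement between arms

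*Protocol article*

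**What the plan says.** All references are to the Methods of the protocol article.

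- **Participant Recruitment and Follow-Up:** "We will include the same participants at baseline and follow-up (a paired sample". Each LGA receives one arm, so there is one LGA per arm in each state and two per arm in all.
- **Data Management and Data Analysis, before-after change:** "We will calculate the percentage change and corresponding 95% CI before and after the interventions are implemented", followed by "the statistical significance of this difference using a z test for differences between proportions".
- **Same section, between arms:** the audio, written and control groups are to be compared by Mann-Whitney, one-tailed t or chi-square tests, with no time point given. The one intervention contrast spelled out is: "We will compare the differences in follow-up assessment between the audio-delivered and written interventions".
- **Same section, modelling:** "Stepwise multivariate regression with backward elimination will be done to examine what factors will have an independent effect on the outcomes", and "If necessary, we will correct for differences in demographic information between study arms using quantile regression".
- **Study Duration and Sample Size Calculation:** the intervention-arm calculation "is based on an estimate of the difference in knowledge improvement between the audio-delivered intervention and the written material intervention groups", with 10% v 25% improvement. For the control arm: "We expect an increase of 2% in the knowledge score in the control group".

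**The concern.** Three things do not fit together.

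1. The design produces pairs, but the named test for change is the usual test for two independent groups. McNemar's test and a paired interval are not mentioned.
2. Change from before to after mixes the intervention effect with anything else that moved over the period. The protocol itself expects some movement in the control arm, and Description of the Intervention promises a comparison with control.
3. The two intervention arms are sized on a between-arm difference in improvement, yet no analysis is said to estimate that. The one named contrast refers to the follow-up assessment and leaves out control. The only stated correction is conditional and covers demographics, not the baseline outcome.

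At stake are precision in the before-after results, and whether the reported effect is protected against background change and against arms that differed at the start.

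**Working it through.** **Step 1. The plan's own figures.** Two independent proportions, unpooled variance, two-sided 0.05, 80% power, 15% loss:

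n = (1.960 + 0.842)² × [p1(1−p1) + p2(1−p2)] / (p1−p2)², then divide by 0.85.

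- 10% v 25%: 7.849 × (0.0900 + 0.1875) / 0.0225 = 96.8; 96.8 / 0.85 = 113.9, so 114 as stated.
- 10% v 2%: 7.849 × (0.0900 + 0.0196) / 0.0064 = 134.4; 134.4 / 0.85 = 158.1, against 157 stated.

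The sample size is not in dispute. Both calculations compare improvement between arms.

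**Inputs for the remaining steps.** From the protocol: 114 per intervention arm per state and 15% loss, so 2 × 114 × 0.85 = 193.8 per arm over both states. Assumed, because the article gives no figure: baseline 40% and baseline/follow-up correlation rho from 0 to 0.7. Clustering is ignored.

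**Step 2. Cost of ignoring the pairing**, for a change from 40% to 50%.

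- Unpaired SE = sqrt[(0.24 + 0.25) / 193.8] = 0.0503.
- Paired SE = sqrt[(0.49 − 2 × rho × sqrt(0.24 × 0.25)) / 193.8].
- The ratio of the two is close to 1/sqrt(1−rho).

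| rho | paired SE | unpaired CI too wide by | real two-sided error of nominal 5% test | power unpaired | power paired |
|---|---|---|---|---|---|
| 0.3 | 0.0421 | 1.20 | 1.9% | 51% | 66% |
| 0.5 | 0.0356 | 1.41 | 0.6% | 52% | 80% |
| 0.7 | 0.0275 | 1.83 | 0.03% | 52% | 95% |

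**Step 3. Background change with no intervention effect.** Chance that the unpaired before-after test is significant in the favourable direction (nominal 2.5%), at rho 0 and rho 0.5:

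- +2 points, the protocol's expectation for control: 5.9% and 1.4%.
- +5 points: 16.8% and 8.7%.
- +10 points: about 51% in both cases.

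**Step 4. A fixed gap between two arms with no effect, compared on follow-up values only.** With one arm at 40% and 193.8 per arm, a gap of 5, 10 or 15 points is significant in 17%, 51% or 84% of trials. The gap sizes are illustrations, not forecasts.

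**Step 5. Which between-arm estimate to use.** For changes of 10 v 25 points:

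- Simple difference in change: power about 57%, 72%, 86% and 97% at rho 0, 0.3, 0.5 and 0.7.
- Follow-up values only: 85%.
- Follow-up adjusted for own baseline (ANCOVA): variance multiplied by 1 − rho², that is 0.91, 0.75 and 0.51 at rho 0.3, 0.5 and 0.7. It does not lose precision at low rho as the simple change does.

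**Step 6. What adjustment leaves behind.** The ANCOVA slope is roughly rho, so about 1 − rho of a persistent LGA gap survives. A 10-point gap leaves about 7, 5 or 3 points at rho 0.3, 0.5 or 0.7. A model with an LGA term has 6 LGAs − 1 intercept − 2 arm terms − 1 state term = 2 between-LGA degrees of freedom.

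**The case against.** The strongest reply is that the article ranks no analysis as primary, and that the section contains more than a z test. It lists tests across all three groups, a regression, effect sizes and a correction for demographic imbalance. The article does not say that the z test is run separately in each arm, that it decides effectiveness, or that follow-up values are used alone. A reader might infer all three, but the text supports none of them outright. The phrase about differences in follow-up assessment could loosely mean change, and the sample-size section makes that a tenable intent. Model covariates may also sit in a fuller document. All of this stands, so it would be wrong to say that no between-arm analysis or comparison with control is planned.

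A reader might also infer that the unpaired test produces false positives. It does not: with positive correlation it is conservative (step 2). At the protocol's own 2% drift the inflation is small or absent (step 3); the larger drifts are assumed. The LGAs in each state are also chosen for similar literacy and endemicity, which limits the gaps to be expected in step 4.

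The reply does not remove the mismatch. A stated test does not fit a stated paired design. None of the other listed analyses is said to use the baseline outcome or to compare improvement between arms. If change is what is meant, the plan should say so.

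**Conclusion.** The point holds as a mismatch between stated method and stated design, and should be fixed.

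- **Pairing:** the before-after interval is about 1.2 to 1.8 times too wide for rho 0.3 to 0.7. At rho 0.5, power for a 10-point change falls from about 80% to 52%. This rests on an assumed baseline of 40%, assumed correlations and no clustering. If LGAs differ in their trends, the stated interval could instead be too narrow.
- **Attribution:** a before-after test cannot separate effect from background change, whatever its variance. The practical risk is small at 2 points and grows with larger drift.
- **Target of estimation:** the intervention arms are sized on between-arm improvement, and no listed analysis is said to deliver it.

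A reader might infer that baseline adjustment would cure imbalance between LGAs. It would not: about 1 − rho of a persistent gap remains, differing LGA trends are untouched, and inference with two LGAs per arm is a separate issue.

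**What to change.** In Data Management and Data Analysis, state that:

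1. The effect estimate is the between-arm difference at follow-up, adjusted for the participant's own baseline value of the same outcome and for state. Use linear regression for scale scores and logistic regression for binary items. Report audio v written, audio v control and written v control.
2. Any before-after description uses McNemar's test or a paired-difference confidence interval in place of the two-proportion z test, and is not presented as evidence of effect.
3. Baseline adjustment reduces but does not remove persistent LGA differences, does not address differing trends, and does not settle inference with two LGAs per arm. How LGA is handled must be stated separately; a random LGA term with about 2 between-LGA degrees of freedom should not be presented as the solution.

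Items 1 and 2 cost only a change of wording. Baseline data on 811 respondents are collected, and the Results section says analysis had not begun at submission. No new data or change in sample size is needed for this point. The few-cluster problem in item 3 may cost more and is not priced here.

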### Ethical Considerations

Ethical approval has been obtained from the Health Research and Ethics Committee of the University of Nigeria Teaching Hospital, Ituku-Ozalla, Enugu (NHREC/05/01/2008B-FWA00002458-1RB00002323). In addition, appropriate clearance was sought and obtained from the respective ethics committees of both the Taraba and Cross Rivers State Ministries of Health. The confidentiality of the study participants and the data collected from them will be ensured.

Written informed consent (Multimedia Appendix 2) will be obtained from the study participants. The questionnaire will be translated into the local languages included in this study and back-translated to ensure the soundness of the translation process. The consent form explicitly states the right of the participant to refuse giving consent or withdraw from the study at any point. Also, he or she can decline to answer any question. Informed consent will be obtained from each participant before participation. Each participant will be given a copy of the participant information sheet and consent form to keep.

This RCT study was prospectively registered with and listed on the Pan African Clinical Trials Registry (PACTR202205543939385).

## Results

This study was funded in June 2022, and community member participant recruitment started in January 2023. Baseline data collection was completed by May 2023, with a total of 811 respondents. Participatory cocreation of the audio and written health education content began in July 2023, and the materials are currently under development. Intervention will be administered after pilot-testing, and the follow-up period will last for 6 months. Neither the implementation of the study intervention nor the data analysis have commenced as of the time of submission. Study results are expected in September 2024.

## Discussion

### Principal Considerations

In this study, we will apply mixed methods to compare the impact of audio-delivered versus written health education intervention materials and a control group without any intervention on the perception (knowledge, beliefs, and attitudes) of community members regarding leprosy. Through a participatory cocreation process, we will develop the content of the intervention materials alongside persons affected by leprosy and implement a 3-arm cluster RCT to evaluate the effect of the intervention. The effect of the cocreation process on internalized stigma among the affected persons will also be evaluated.

Developing context-specific behavioral change intervention activities is critical to addressing stigma in many leprosy-endemic communities where leprosy is highly stigmatized. The outcome of this intervention is expected to influence knowledge and, hopefully, improve the attitudes of community members toward leprosy, as well as improve self-esteem among persons affected by leprosy. In the long run, early leprosy case finding will be boosted following stigma reduction. To the best of our knowledge, this is the first study of this kind in Nigeria. The generated educational materials (both the audio and written content) are reusable products that may be adopted or used by the national program. The audio-delivered educational content will be freely available on the Audiopedia platform, licensed under Creative Commons (CC BY).

### Limitations

There are inherent limitations associated with cluster-randomized studies, such as cluster size variability. With the challenge of achieving uniform cluster sizes, variability in cluster size could impact the generalizability of the results. Additionally, there is a risk of contamination between clusters; however, this is minimal given the geographic distance between the study cluster locations.

The study sites were purposefully selected due to their similarity in having a high prevalence of leprosy and G2Ds; thus, the findings from this study may not be generalizable to the entire Nigerian populace.

### Conclusion

Outputs from the research will offer policy makers, national and regional program managers, and partners reliable evidence for a new approach toward stigma reduction activities, thereby contributing toward global triple zero leprosy efforts. Content generated provides pragmatic and contextual evidence-based tools for effective health education campaigns and awareness creation, especially among populations with low literacy levels, both in Nigeria and other low- and middle-income countries.

## Appendix

Multimedia Appendix 1 SPIRIT 2013 Checklist: Recommended items to address in a clinical trial protocol and related documents.

Multimedia Appendix 2 Participant information sheet and informed consent form.

Multimedia Appendix 3 Peer review report by Leprosy Research Initiative (LRI), Amsterdam, The Netherlands.

## Abbreviations

6SQuID: 6 steps in quality intervention development
EMIC-CSS: Explanatory Model Interview Catalogue Community Stigma Scale
FGD: focus group discussion
G2D: grade 2 disability
ISMI: Internalized Stigma of Mental Illness scale
KAP: knowledge, attitudes, and practices
LGA: local government area
RCT: randomized controlled trial
RSES: Rosenberg Self-Esteem Scale
SDS: Social Distance Scale
WHO: World Health Organization
